### Outcome measures

Length of stay will be the primary outcome. A standardized and objective decision rule will be used for hospital discharge. All of the following criteria will be required for discharge: (1) off oxygen for at least 24 hours (requires saturation ≥90 % on room air); (2) absence of fever for 24 hours; (3) vital signs stable; and (4) drinking and/or breastfeeding well.

Several secondary outcomes will be recorded. Patient-specific outcomes will be measured in each group: mortality, proportion of patients successfully oxygenated, duration of oxygen therapy, and clinical severity score. The proportion of patients successfully oxygenated will be defined as the number of patients who achieve a saturation ≥90 % for ≥12 hours after initiating oxygen therapy. The clinical severity scores used will be the previously published and validated Lambaréné Organ Dysfunction Score (LODS) [10] and the Respiratory Index of Severity in Children (RISC) [11].

Oxygen delivery system variables will include direct costs (capital investment, operating costs, system maintenance, *etcetera*), details of maintenance needs, convenience of use of the systems and proportion of patients for whom the delivery system failed. System failure will be defined as inadequate oxygen production to meet patient needs for any reason. Examples would include battery failure for SPO2 or out-of-stock cylinder oxygen.

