### Safety

Oxygen therapy is known to be a life-saving intervention, and this study will improve hospital capacity for the treatment of hypoxemic children. While patients will be randomized to one of two possible oxygen delivery systems, there are no risks, and benefits include potentially life-saving access to oxygen, regardless of delivery modality. Study participants will be managed at the Jinja Regional Referral Hospital according to national guidelines and local clinical practices. Outcome assessment in the study will not pose any risk to the study participants.

Adverse events, defined according to Good Clinical Practice (GCP) guidelines as any untoward event occurring in a study participant, will be logged prospectively and tabulated at the end of the study, disaggregated by study arm. Severe adverse events, defined as those adverse events that prolong hospitalization or lead to permanent disability or death, will be reported to regulatory authorities in an expedited manner and reported separately in the safety analysis.

This study involves hypoxemic patients with severe pneumonia or very severe disease, and the mortality is expected to be high because of the underlying illness. Mortality among patients receiving SPO2 will to be interpreted in comparison to patients receiving O_2_ by standard method (cylinders).

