### Sample size calculations

We will enroll a total of 130 patients. This sample size was calculated as follows. A 1:1 ratio of patients will be assigned to SPO2 or control (cylinder O_2_). We consider a 1-day prolongation of hospital stay to be clinically significant (noninferiority margin). Using pilot data from a prospective study at Jinja Regional Referral Hospital, 69 patients with hypoxic pneumonia had a mean (standard deviation) length of stay of 2.6 (2.1) days (unpublished data). By standard calculations for normally distributed data, 57 patients in each group will provide 80 % power to demonstrate noninferiority of SPO2 relative to oxygen by cylinder at α = 0.05 (one-sided). This sample size was increased by 15 % to account for a probable non-Gaussian distribution of the data [12].

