### Primary analysis

Length of stay (in days) will be coded as a whole number (continuous variable). Difference in length of stay between groups will be compared using the nonparametric method of Hodges and Lehman. If the *a priori* noninferiority margin (Δ = 1 day) is below the lower limit of the 95 % confidence interval for the median of differences, the trial will conclude that SPO2 is noninferior to cylinder oxygen. In order to account for all patients randomized (“intention-to-treat” analysis), we will perform sensitivity analyses to account for missing data due to mortality, study withdrawal, and transfer to another facility. A *per protocol* population (non-fatal cases discharged home from hospital) will be used to assess the robustness of the primary result (non-inferiority). Details of the sensitivity analyses will be included in a Statistical Analysis Plan, which will be closed as early as possible in the conduct of the trial.

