### Secondary outcomes

The mortality will be compared between groups using the chi-squared statistic, or Fisher’s exact test, as appropriate. The proportion of patients successfully oxygenated and proportion of patients for whom the oxygen delivery system failed will be analyzed in a similar manner. The duration of oxygen therapy will be compared using nonparametric methods (Mann-Whitney U-test) and/or Cox-proportional hazard models. Costs will be carefully tabulated (capital investment, ongoing costs, and system maintenance, *etcetera*) and summarized for each group of patients. Details of maintenance needs and convenience of use of the systems will be documented and tabulated. The LODS and RISC (clinical severity scores) will be assessed and recorded serially over the course of hospital admission; comparison between groups will make use of linear mixed effects models to compare the longitudinal time course of the clinical severity score during convalescence.

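### The 'per protocol' set is defined by survival and discharge home, so it cannot show whether noninferiority is robust to departures from the assigned oxygen system

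*Protocol article*

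**What the plan says.** Protocol article, Primary analysis: the per protocol "population (non-fatal cases discharged home from hospital) will be used to assess the robustness of the primary result (non-inferiority". The sentence before it covers the all-randomized analysis: "we will perform sensitivity analyses to account for missing data due to mortality, study withdrawal, and transfer to another facility". The section then defers further detail: "Details of the sensitivity analyses will be included in a Statistical Analysis Plan". The deferral concerns details; the rule for membership of the per protocol set is stated in the protocol itself.

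Outcome measures foresees supply failures in both arms: "System failure will be defined as inadequate oxygen production to meet patient needs for any reason". It adds: "Examples would include battery failure for SPO2 or out-of-stock cylinder oxygen". Under Secondary outcomes, failure enters the analysis only as a comparison between arms: the "proportion of patients for whom the oxygen delivery system failed will be analyzed in a similar manner" as mortality.

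Safety says that "the mortality is expected to be high because of the underlying illness", without giving a rate. Sample size calculations sets the margin: "We consider a 1-day prolongation of hospital stay to be clinically significant (noninferiority margin".

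**The concern.** In a noninferiority trial, departures from assigned treatment usually pull the arms together, which favours the conclusion the trial hopes to reach. A per protocol analysis is normally added as a check on this, so its membership should depend on eligibility and on treatment received. Here neither criterion does. The set is one of survivors and completers under a per protocol label.

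Two things are at stake. First, a reader who sees the per protocol result agree with the main result may take it as evidence that departures from the assigned system did not matter, which this set cannot show. Second, death and transfer are events that oxygen delivery could affect. If they differ by arm, the remaining children are no longer a randomized comparison.

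**Working it through.** **1. What each planned analysis addresses**

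| Analysis in the protocol | Addresses death, withdrawal, transfer | Addresses departure from the assigned oxygen source |
|---|---|---|
| All-randomized, with sensitivity analyses (Primary analysis) | Yes | No |
| 'Per protocol': survived and discharged home (Primary analysis) | Yes, by exclusion | No |
| System failure by arm (Secondary outcomes) | No | Counts failures; does not relate them to length of stay |

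No row tests whether the length-of-stay result is robust to departures from the assigned source.

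**2. The plan's own figure**

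Inputs from Sample size calculations: margin 1 day, SD 2.1 days, one-sided α 0.05, power 80%, true difference 0.

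n per arm = 2 × 2.1² × (1.645 + 0.842)² / 1² = 54.5, so 55; the t-based version needs 56. The protocol states 57, which reproduces within 2. Inflation: 57 × 1.15 = 65.55 per arm, or 131.1 in total, against 130 stated. The concern does not depend on this figure, but it gives about 65 per arm for the illustrations below.

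**3. Dilution if children switch (illustration; switching rates assumed)**

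Suppose SPO2 truly adds 1 day and a fraction f of SPO2 children takes on the cylinder-arm stay in full after a switch. The expected difference becomes 1 − f. The standard error is 2.1 × √(2/65) = 0.368. The chance of a false noninferiority conclusion is Φ(f/0.368 − 1.645).

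| f | f/0.368 − 1.645 | False noninferiority |
|---|---|---|
| 0 | −1.645 | 5.0% |
| 5% | −1.509 | 6.6% |
| 10% | −1.374 | 8.5% |
| 20% | −1.102 | 13.5% |
| 30% | −0.831 | 20.3% |

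All such children who survive and go home stay in the protocol's per protocol set.

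These percentages depend heavily on the model:
- Simulated Hodges-Lehmann limits with continuous gamma or lognormal stays (mean 2.6, SD 2.1) give 9-10%, 15-20% and 28-31% at f = 10%, 20% and 30%. Repeat runs agree within a few percentage points.
- The protocol codes stay in whole days. With stays rounded up and a limit strictly below 1 required, the same scenarios give about 1% or less.
- If a switch removes only half of the effect, 30% switching gives 12-16% with continuous stays.

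**4. Selection on survival (illustration; death rates assumed)**

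Stays were simulated with the same distribution in both arms, and with sicker children both staying longer and dying more often. Deaths were about 10% on cylinder.

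| Deaths on SPO2 | Mean difference among survivors, SPO2 minus cylinder |
|---|---|
| About 10% | 0.00 day |
| About 17% | −0.08 day |
| About 24% | −0.15 day |

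The shift favours SPO2. It is small against a 1-day margin but goes in the unsafe direction.

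**5. Size of a set defined by treatment received (same approximation; exclusions assumed equal in both arms)**

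- 10% lost to death, transfer or withdrawal, and 10% of the rest to switching: 65 × 0.9 × 0.9 = 52.7 per arm; power 79%.
- 20% and 20%: 65 × 0.8 × 0.8 = 41.6 per arm; power 70%.
- For comparison, the full 65 per arm: 86%.

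**The case against.** **The set does have a use.** The preceding sentence names missing stays from death, withdrawal and transfer as the problem, and this set consists of children whose stay ended in discharge home. Comparing it with the all-randomized result tests the handling of those events. This stands. A reader might infer that the set cannot test robustness at all; the protocol does not support that. It is silent only on departures from the assigned source.

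**Switching is not described.** A reader might infer from the system-failure definition that children are moved to the other source and counted as clean SPO2 stays. The protocol defines failure but never says what a child then receives, or how often. This also stands: the point concerns what the set would retain if switching occurs.

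**The error rates do not describe this plan.** It is tempting to quote a false-conclusion risk of around 30% instead of 5%. That needs assumed 30% switching, complete loss of the SPO2 effect after a switch, and continuous stays. With whole-day coding the inflation nearly disappears. The simulations also included no deaths or transfers, so they cannot show how the survivors' set would behave.

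**Failure is part of the strategy.** The Discussion wants data on the system under field conditions, so children whose SPO2 system failed belong in their assigned arm, and excluding them can favour SPO2. This is right for the all-randomized analysis, and it is why a set based on treatment received can only be supportive. It does not justify the present label.

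**The SAP may add criteria, and failures are reported by arm.** The SAP is not shown, but the membership rule is already fixed in the protocol. A count of failures shows how much switching was possible, not whether it affected the length-of-stay result.

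**Conclusion.** The concern holds in a limited form. The protocol gives the per protocol label to a set chosen by outcomes after randomization. That set serves as a sensitivity analysis for the handling of deaths, withdrawals and transfers. It does not serve as a check on departures from the assigned oxygen system, and no other analysis in the protocol fills that gap, although failures are foreseen in both arms. Selection on survival and discharge is a second weakness, and it matters only if these differ by arm.

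The defect in the definition follows from the text and needs no assumption. Its numerical consequence cannot be established: no crossover rule, switching rate or death rate is given, and the illustrative risks run from about 1% or less to about 30% depending on the coding of stay and the assumptions about switching. The correction is worth making because it is cheap and standard for a noninferiority trial, not because a particular error rate has been shown.

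**What to change.** 1. Rename the current set 'survivors discharged home' and keep it as a missing-data sensitivity analysis.
2. Add a supportive per protocol set defined by eligibility and receipt of the assigned oxygen source. Before the SAP closes, prespecify how system failures and changes of source are treated in the analysis. This is an analysis rule only; it implies nothing about how a failure should be managed clinically.
3. Read that set beside the all-randomized analysis, which keeps system failures in their assigned arm, and report the number of children switched in each arm.

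Ranking deaths as the worst outcome, or requiring the same conclusion in both sets, are options for the trial team and are not needed for this correction.

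The cost is SAP wording and a record of the oxygen source for each child; system failure is already recorded per patient as a secondary outcome. The downside is a smaller set with selection of its own. Removing children whose SPO2 system failed can favour SPO2, so the new set should not replace the all-randomized result.

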### Secondary outcomes

The mortality will be compared between groups using the chi-squared statistic, or Fisher’s exact test, as appropriate. The proportion of patients successfully oxygenated and proportion of patients for whom the oxygen delivery system failed will be analyzed in a similar manner. The duration of oxygen therapy will be compared using nonparametric methods (Mann-Whitney U-test) and/or Cox-proportional hazard models. Costs will be carefully tabulated (capital investment, ongoing costs, and system maintenance, *etcetera*) and summarized for each group of patients. Details of maintenance needs and convenience of use of the systems will be documented and tabulated. The LODS and RISC (clinical severity scores) will be assessed and recorded serially over the course of hospital admission; comparison between groups will make use of linear mixed effects models to compare the longitudinal time course of the clinical severity score during convalescence.

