#### Exclusion criteria

Exclusion criteria include the following:Outside eligible age rangePeripheral oxygen saturation ≥90 %Suspected pulmonary tuberculosisOutpatient managementDenial of consent to participate in studyTrial inpatient capacity exceeded

The reason for exclusion of patients with pulmonary tuberculosis is for infection control, in order to avoid the risk of transmitting tuberculosis to other patients housed in the study unit. The trial inpatient capacity at each study site is two beds with a concentrator and two beds with a cylinder. In cases where two patients are already enrolled in the same arm, subsequent patients will not be enrolled because of the potential inability to randomize to the occupied beds.

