### Study setting

The trial will take place at two hospitals in Uganda: (1) the Jinja Regional Referral Hospital is located in in mid-eastern Uganda, which serves a large catchment area in the Busoga Region, and (2) Kambuga Hospital in Western Uganda, a remote site with limited road access. Both are severely resource-limited hospitals with inconsistent electrical power supply, and both were using oxygen from cylinders and concentrators at the time of study planning. Uganda has a high burden of child mortality and pneumonia: the under-five mortality rate in 2008 was 135 deaths per 1000 (19^th^ highest rate worldwide), and pneumonia is the fourth leading cause of mortality in Ugandan children under five (11 %) [1].

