### Treatment groups

Children will be randomly assigned to receive oxygen using either SPO2 or cylinder oxygen in a 1:1 ratio.

The intervention arm is oxygen from a solar-powered concentrator. The SPO2 systems, which are built in Jinja and Kambuga, consist of photoelectric panels (80 W or 175 W panels, Solarworld, Freiburg, Germany), charge controller (FLEXmax 80, OutBack Power, Arlington, WA, USA or 40 A/24 V Controller, Steca Elektronik GmbH, Memmingen, Germany), bank of gel batteries (220 Ah/12 V UltraPower gel batteries, Victron Energy BV, Almere Haven, The Netherlands), power inverter (3000 VA/48 V Inverter/Charger or 1600 VA/24 V Inverter/Charger, Victron Energy BV, Almere Haven, The Netherlands) and oxygen concentrator (model 525 KS, DeVilbiss Healthcare LLC, Somerset, PA, USA). The system is designed to run independently of hydroelectric power source (exclusively driven by solar energy), and provide continuous uninterrupted oxygen (up to 5 L/min) throughout both day and night (using energy stored in battery bank). The total cost of each system was approximately US $18,000.

The control arm consists of oxygen in a cylinder with flow regulator, tubing and nasal prongs or mask for delivery to the patient. Cylinders (pressure, capacity) can be purchased from commercial suppliers in Uganda (Oxygas, Kampala, Uganda) at a cost of US $200 and are refillable at a cost of US $14. In addition, a regulator (US $200) is needed. On average, one pediatric patient with pneumonia will consume approximately 1-6 cylinders of oxygen during the course of hospitalization for pneumonia. In order to have a reliable supply of oxygen, given procurement and transport times, we estimate that six cylinders need to be stocked on the hospital premises.

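### The per-child chi-squared or Fisher test of delivery system failure can overstate the evidence on reliability when one outage affects several children

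*Protocol article*

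**What the plan says.** The Secondary outcomes section has mortality "compared between groups using the chi-squared statistic" or by Fisher's exact test, and continues: "The proportion of patients successfully oxygenated and proportion of patients for whom the oxygen delivery system failed will be analyzed in a similar manner". The unit is therefore the child, and the test treats children as independent.

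The Outcome measures section lists system failure with the delivery-system variables (costs, maintenance, convenience), apart from the patient-specific outcomes. It defines it thus: "System failure will be defined as inadequate oxygen production to meet patient needs for any reason". It adds: "Examples would include battery failure for SPO2 or out-of-stock cylinder oxygen".

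Three other places bear on who shares a supply:

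- Exclusion criteria: "The trial inpatient capacity at each study site is two beds with a concentrator and two beds with a cylinder". Enrolment stops when both beds of an arm are taken. No rule is given for an outage.
- Treatment groups, cylinders: "we estimate that six cylinders need to be stocked on the hospital premises". The stock is held per hospital.
- Treatment groups, solar: "The SPO2 systems, which are built in Jinja and Kambuga, consist of photoelectric panels". Each system has a battery bank, but the number of systems per site is not given.

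**The concern.** A chi-squared or Fisher test on 65 children per arm takes each failure as a separate piece of evidence. A stock-out is one event of one hospital's store. It can count as a failure for both children in the cylinder beds and for any child admitted to that arm before the store is refilled. A battery failure may act in the same way on the solar side. Individual randomization does not remove this, because the common cause acts within the arm.

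Reliability of supply is a practical question behind scale-up, and system failure is the outcome that addresses it most directly. A few outages that happen to fall in one arm could be reported as a statistically significant difference in reliability, in either direction, when the underlying outage rates are equal.

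**Working it through.** **Inputs from the article.** 130 children, 1:1, so 65 per arm; two sites ("The trial will take place at two hospitals in Uganda"); two beds per arm per site; length of stay mean 2.6, SD 2.1 days (Sample size calculations).

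**The plan's own figure.** No figure is given for the system-failure test. The primary sample size reproduces closely: n per arm = 2(1.645 + 0.842)² × 2.1² / 1² = 54.5, so 55 (56 with the t distribution), against 57 stated; 57 × 1.15 × 2 = 131.1 against 130.

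**Step 1: what a few outages look like to the planned test.**

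- Suppose three brief outages occur in one arm, each affecting the two children in its beds, and none in the other arm. The test sees 6/65 v 0/65: Fisher p = 0.028, uncorrected chi-squared p = 0.012. Counted as outages the evidence is 3 v 0, and with equal exposure the exact conditional p = 2 × 0.5³ = 0.25.
- Suppose one 7-day outage, with both beds always full and admissions continuing. It touches about 2 + 2 × 7/2.6 = 7.4 children. Taking 7/65 v 0/65, Fisher p = 0.013 from a single event.

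**Step 2: design effect for small clusters.** DE = 1 + (m − 1) × ICC; true two-sided error = 2 × P(Z > 1.96/√DE). The ICC is assumed.

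| Children per outage (m) | ICC | DE | True error |
|---|---|---|---|
| 2 | 0.25 | 1.25 | 0.08 |
| 2 | 0.5 | 1.5 | 0.11 |
| 2 | 1 | 2 | 0.17 |
| 4 | 0.5 | 2.5 | 0.22 |
| 4 | 1 | 4 | 0.33 |

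Two is the most that can be affected at one moment in an arm at a site. Larger m needs an outage that lasts into later admissions.

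**Step 3: simulation under equal outage rates.** Assumed: one shared supply per arm per site, down 10% of the time; random outages with exponential duration; blocks of 4; gamma stay with the mean and SD above, used as time at risk; the article's capacity rule; a child fails if the stay overlaps an outage; enrolment continues during outages. Share of Fisher tests with p < 0.05:

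| Mean outage | 0.15 arrivals/day/site | 0.3 | 0.6 |
|---|---|---|---|
| 1 day | 0.053 | 0.080 | 0.092 |
| 3 days | 0.072 | 0.103 | 0.135 |
| 7 days | 0.101 | 0.172 | 0.242 |
| 14 days | 0.172 | 0.287 | 0.358 |

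Over repeated runs the ranges are about 0.04-0.11 (1 day), 0.06-0.17 (3 days), 0.10-0.26 (7 days) and 0.17-0.38 (14 days).

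**Step 4: two assumptions changed.**

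- Enrolment paused at a site while either arm's supply is down, supply still shared: Fisher's error is 0.044-0.064 (1 day), 0.039-0.051 (3 days), 0.020-0.033 (7 days) and 0.001-0.006 (14 days). The inflation is gone.
- Each bed with its own independent supply, enrolment continuing, arrivals 0.15 to 1.0 per day per site, mean time between failures 30 days (60 for the 7-day case), and Fisher or chi-squared chosen by expected counts: 0.043-0.063 for outages of a day or less, 0.05-0.10 for 3 days, 0.09-0.19 for 7 days.

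**The case against.** Several objections have force.

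- **Sharing is not established throughout.** A reader might infer that any outage hits every child on that arm at that site. That is clear for a stock-out. For a battery failure it is only an inference: the article speaks of systems in the plural and does not say whether the two solar beds share a battery bank.
- **Some failures belong to one child.** The definition admits any cause, so one child's need exceeding a device's output, or one faulty regulator, also counts. Such failures are not shared, and the simulation leaves them out.
- **The inflation depends on enrolment during outages.** Step 4 shows that a pause removes it. The article states no pause, but it also does not say that children are randomized to a supply that is down.
- **The stated outcome is the proportion of children affected.** Given the outages that occurred, randomization keeps Fisher's test valid for whether assignment made a difference to these children. The p-value misleads only when it is read as evidence on how reliable the two technologies are. The Discussion's interest in scale-up invites that reading, but the article states no decision rule based on it.
- **A larger figure is tempting.** Treating all 32.5 children in an arm at a site as one cluster with ICC 0.05 gives DE = 1 + 31.5 × 0.05 = 2.58 and an error of about 22%. Nothing in the article supports that ICC, or a cluster that lasts the whole trial; two children at the same ICC give 5.6%.

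These objections limit the size and certainty of the point. They do not remove it: the article fixes a per-child test, gives supply-level examples, and makes no allowance for children who share a failure. Shared outages could also bear on successful oxygenation or length of stay; that was not worked through, and nothing is claimed about it.

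**Conclusion.** The point holds in a conditional form. Where one outage affects several children, the planned p-value can be too small as evidence about system reliability. The documents do not support the flat statement that it is too small.

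With a shared supply, 10% downtime and continued enrolment, all assumed, the nominal 0.05 Fisher test has a true error of about 0.04-0.11 for 1-day, 0.06-0.17 for 3-day and 0.10-0.26 for 7-day outages. It is about nominal or below if enrolment pauses during outages, and the excess can be negligible if outages are rare and brief. This is one of several secondary outcomes; the primary analysis and the sample size need no change on this account.

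**What to change.** In the Secondary outcomes section, take system failure out of the sentence that gives it the same analysis as mortality, and state instead:

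1. The proportion of children affected is reported by arm and site as a descriptive figure, with no chi-squared or Fisher claim about reliability.
2. The number of distinct failure episodes and their duration are reported by arm and site, with the number of children affected by each.
3. Any between-arm comparison of reliability rests on distinct episodes per period of operation, as a site-stratified rate ratio with an exact interval, or on an analysis clustered by episode. The period of operation needs a definition for a rotating cylinder stock.

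It would also help to state whether the two solar beds at a site share a battery bank and whether enrolment continues during an outage.

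The cost is a few sentences and possibly a log of outage start and end times, which the article does not mention. The interval will be wide when outages are few. An episode count treats short and long outages alike, which is why duration should be reported beside it.

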### Study objectives

The overall objective is to demonstrate the noninferiority of solar-powered oxygen delivery relative to standard oxygen delivery. Specifically, we will compare the length of stay in children hospitalized with acute hypoxic respiratory illness randomized to SPO2 versus cylinder oxygen. The working hypothesis is that the length of stay is not increased in children treated with SPO2 compared to children receiving cylinder oxygen. Secondary outcomes will be compared between groups, including patient-specific outcomes (mortality, duration of supplemental oxygen therapy (time to wean O_2_), proportion of patients successfully oxygenated, and clinical severity scores) and oxygen delivery system indicators (system failures, cost, maintenance and convenience of use).

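### Time to wean oxygen is to be compared by Mann-Whitney and/or Cox with no stated place for death, so the result can favour the arm with more deaths if deaths enter at their observed oxygen time

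*Protocol article*

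**What the plan says.** The Study objectives section of the protocol article lists among the secondary outcomes "duration of supplemental oxygen therapy (time to wean O_2", so the quantity of interest is weaning and not simply hours on oxygen. The Abstract gives the same gloss. The Secondary outcomes section then fixes the comparison: "The duration of oxygen therapy will be compared using nonparametric methods (Mann-Whitney U-test) and/or Cox-proportional hazard models".

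Two other statements bear on this. Under Safety, "the mortality is expected to be high because of the underlying illness". Under Secondary outcomes, death has its own test: "The mortality will be compared between groups using the chi-squared statistic, or Fisher’s exact test, as appropriate".

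The only provision for deaths in a duration outcome is under Primary analysis: "we will perform sensitivity analyses to account for missing data due to mortality, study withdrawal, and transfer to another facility". It is accompanied by a population of non-fatal cases discharged home. Both concern length of stay. The article adds that "Details of the sensitivity analyses will be included in a Statistical Analysis Plan"; that plan is not at hand. Nothing in the article says how a child who dies on oxygen enters the comparison of oxygen duration.

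**The concern.** Oxygen stops for two opposite reasons: the child no longer needs it, or the child dies. A Mann-Whitney test on duration of oxygen sees only when it stopped. The test therefore needs a rule for deaths, and the two simplest choices are both poor:

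- All randomized children with observed oxygen time: a death a few hours after admission takes one of the best ranks.
- Survivors only: no death is misranked, but the groups compared are defined by an event after randomization and are no longer the randomized groups.

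A Cox model behaves differently. If the end of oxygen for any reason is the event, a death counts as a success. If deaths are censored, a death is not a wean, and the model estimates the cause-specific hazard of weaning. That is a legitimate quantity, but it does not by itself show what proportion of children have been weaned by a given time.

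Linking the two methods by and/or leaves open which of these quantities will be reported. At stake is a secondary outcome that could be read as support for one delivery system when it partly reflects earlier death in that arm.

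**Working it through.** **Plan's own figures.** The article gives no figure for the oxygen-duration comparison and no mortality rate. The size used here is the planned total ("We will enroll a total of 130 patients"), allocated 1:1, so 65 per arm. The stated sample size for length of stay approximately reproduces: 2 × 2.1² × (1.645 + 0.842)² / 1² = 54.5, so 55 per group (56 with the t distribution) against 57 stated. It is unaffected by this point.

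**How high might mortality be?** The Discussion gives 1,134 per group for noninferiority on mortality within 5 percentage points. With equal rates p, n = 2p(1 − p)(z_α + z_β)² / 0.05². The power and alpha behind that figure are not stated, so conventional values are assumed:

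- One-sided 0.05, 80% power: p(1 − p) = 1,134 × 0.0025 / (2 × 6.18) = 0.229, so p ≈ 36%.
- One-sided 0.025, 90% power: p(1 − p) = 2.835 / (2 × 10.51) = 0.135, so p ≈ 16%.

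Death rates of 10% to 30% are therefore not far-fetched, but they remain assumptions.

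**Direction of the distortion.** Let weaning times have the same distribution in both arms, let death be independent of the child's potential weaning time, and let the death proportions be p_S (SPO2) and p_C (cylinder). Let q be the chance that the recorded time of a child who dies exceeds that of an independent child who weans. Adding up the four pairings (both wean, both die, only one dies) gives

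P(SPO2 child has the longer time) = 0.5 + (p_S − p_C)(q − 0.5).

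- Death ranked worst: q = 1, so P = 0.5 + (p_S − p_C)/2. At 10% (cylinder) versus 20% (SPO2) this is 0.55; at 10% versus 30% it is 0.60.
- Observed oxygen time: q depends on when deaths occur. Assume lognormal duration with mean 1.6 and SD 1.6 days, and death at a uniformly random fraction of that course. Then s² = 2 ln 2 = 1.386, s = 1.177, and q = 0.5 − e^(s²/2) Φ(−s) = 0.5 − 2 × 0.1195 = 0.261. So P = 0.5 − 0.10 × 0.239 = 0.476 at 10% versus 20%, and 0.5 − 0.20 × 0.239 = 0.452 at 10% versus 30%. Simulation gives 0.477 and 0.454.

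The two codings point in opposite directions. The formula also gives the limits: no shift if p_S = p_C, and the raw ranking favours the higher-mortality arm only if deaths tend to come earlier than weaning (q < 0.5).

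**How often it would mislead.** 4,000 simulated trials per scenario, 65 per arm, two-sided Mann-Whitney at 5%, identical weaning. The false-shorter rate is the share of trials in which oxygen time is declared significantly shorter in the higher-mortality arm (nominal 2.5%).

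Same model, observed oxygen times:

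- 10% v 10% and 20% v 20%: 5.3% and 4.5% significant in either direction (nominal 5%).
- 10% v 15%: 4.4% false-shorter.
- 10% v 20%: about 7%.
- 10% v 30%: about 14% (simulation error √(0.14 × 0.86 / 4,000) ≈ 0.6 points).

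Second model (lognormal weaning, mean 2 days, CV 0.8; time to death exponential, mean 0.75 day), observed oxygen times:

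- 5% v 5%: 2.8%.
- 5% v 10%: 5.0%.
- 10% v 20%: 9.1%.
- 5% v 20%: 14.6%.
- 10% v 30%: 24.3%.

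In the second model, ranking death worst brings the false-shorter rate to at most 0.6% in the unequal scenarios. A survivors-only test stays at 2.2% to 2.7% in each direction, but only because the simulation makes death independent of weaning time. If sicker children both die more and wean later, that protection is not assured.

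**The case against.** The strongest reply is that the article names candidate tests and does not state a coding for deaths. A reader might infer that a child who dies early will be ranked as a fast wean. The article does not say so: that follows only if all children enter Mann-Whitney with death ending the duration. Coding of deaths for a secondary outcome is normally left to the analysis plan, and the authors clearly saw the issue for length of stay. This stands, and the point is therefore conditional. What remains is that the article itself names a rank test on duration for an endpoint it defines as weaning, and that its provision for deaths is tied to length of stay.

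A reader might extend the same criticism to Cox. It does not carry over to a Cox model that censors deaths, which counts no death as a wean.

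A reader might also infer that the method will be picked once open-label results are seen. The article does not support that: it intends to close the analysis plan early, and that plan may settle the choice.

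The size is also fairly contested. It rests on assumed inputs, is nil with equal deaths and modest when mortality doubles, and a threefold difference in deaths would show in the separate mortality comparison and the adverse event tables by arm. All of that stands. It limits the weight of the point but does not make the rank test on raw durations a sound measure of weaning.

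**Conclusion.** The point holds in conditional form and should be acted on, at the level of a secondary outcome. Mann-Whitney on observed oxygen time cannot distinguish weaning from death, in a population where the article itself expects many deaths. If deaths differ between arms and tend to come early, the comparison shifts towards the arm with more deaths. The false-shorter rate is about 7% at 10% versus 20% deaths and about 14% at 10% versus 30% under the first model, and 9% and 24% under the second, against 2.5%. These figures assume the death rates and timing, identical weaning in both arms, and deaths entered at observed oxygen time; the article fixes none of these.

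With equal deaths in number and timing there is no material bias. The noninferiority conclusion on length of stay and the sample size are unaffected. It would go too far to call this outcome the one closest to the mechanism under test: successful oxygenation and system failure measure oxygen delivery more directly.

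**What to change.** Replace the and/or sentence, in the analysis plan or by amendment, with one analysis: time from start of oxygen to successful weaning, in all randomized children, with death before weaning never counted as a wean. Either of these would serve:

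- cumulative incidence of weaning by arm, with death before weaning as a competing event; or
- a rank test in which death before weaning takes the worst rank.

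Report the result beside mortality. If a Cox model censoring deaths is kept, label it a cause-specific hazard of weaning.

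The cost is a few lines of text. No extra patients are needed, and the outcomes required (oxygen duration and death) are already to be recorded. Recruitment was ongoing at publication, so the rule could be set before analysis. The small downside is that a worst-rank result is a composite of death and duration: it partly repeats the mortality comparison and must be read as such.
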